### Sample size

Power analysis was performed for the primary outcome measure (Step Quick Turn test on the Neurocom® Balance Master), using the mean score for the Step Quick Turn test (sway-degrees/s) results from a previous exercise intervention trial of older people with mild balance impairments [34]. It was estimated that 34 participants per group (68 participants in total) would be required to have at least 80% power to detect a 15% improvement in the Step Quick Turn test using the turn sway measure on the Neurocom Balance Master long-plate (degrees/s), (assuming 50% standard deviation improvement with the intervention [sd = 10.2, effect size = 0.5] at P < 0.05 (two-tailed). This calculation includes allowance for an anticipated 20% dropout rate. This sample size should also be adequate for other secondary outcome measures including the Limits of Stability test (Neurocom® Balance Master), the Step Test, and Functional Reach Test.

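### The stated 34 per group cannot be reproduced from the protocol's own inputs for a two-group comparison, and the 20% dropout allowance does not fit those inputs

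*Protocol article*

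**What the plan says.** The Sample size section sizes the trial on Step Quick Turn sway: "34 participants per group (68 participants in total) would be required to have at least 80% power to detect a 15% improvement". The effect is given as "assuming 50% standard deviation improvement with the intervention", with "sd = 10.2, effect size = 0.5", tested "at P < 0.05 (two-tailed". On attrition it says "This calculation includes allowance for an anticipated 20% dropout rate". It then extends the number further: "This sample size should also be adequate for other secondary outcome measures", naming Limits of Stability, the Step Test and Functional Reach.

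The Randomization section allocates participants to exercise or control. The Statistical analysis section compares the two groups over two time points by two-way repeated measures ANOVA, including the group-by-time interaction, on an intention-to-treat basis. The Missing data section fills in losses to follow-up by carrying the last value forward. Nowhere does the article give a baseline to 16-week correlation, say whether 10.2 is the SD of a single measurement or of change, or name the test behind the power calculation.

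**The concern.** Half a standard deviation is a familiar benchmark. At a two-sided 5% level and 80% power it calls for a little over 60 per group in a two-group comparison, before dropout. A figure of 34 that is said to include dropout already is about half of that. The gap is too large for rounding or for a normal approximation in place of the t distribution (63 against 64 per group).

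At stake is how a primary outcome will be read. The article concedes low power only for falls, so a reader will take 80% for turning sway at face value. If the true power for the stated effect is well below that, a non-significant result says much less about the programme than the protocol implies.

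**Working it through.** **Inputs** (all from Sample size): standardised effect d = 0.5; SD = 10.2 deg/s; two-sided alpha 0.05; power 0.80; dropout 20%; 34 per group. The absolute effect is 0.5 × 10.2 = 5.1 deg/s. If that is 15% of the mean, the implied mean is 5.1 / 0.15 = 34.0 deg/s; the mean itself is not stated. With 20% loss, 34 × 0.8 = 27.2, so about 27 complete per group.

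**1. Can 34 be reproduced?** (t-test sizes from the noncentral t distribution)

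| Calculation, d = 0.5, 80% power | n before dropout | n / 0.8 |
|---|---|---|
| Two-sample, two-sided | 63.8, so 64 per group | 80 |
| Two-sample, one-sided | 51 per group | 64 |
| Paired or one-sample, two-sided | 33.4, so 34 | 42.5, so 43 |
| Paired or one-sample, one-sided | 26.1, so 27 | 33.75, so 34 |

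The normal-approximation check for the first row is 2 × (1.96 + 0.842)² / 0.5² = 62.8, so 63.

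Under the stated two-tailed level, 34 appears only as the paired size with nothing added for dropout. With 27 completers even that within-group test has 71% power. It appears with a 20% allowance only for a one-sided paired test, which contradicts both the stated sidedness and the two-group design. Two other routes give 34 before dropout, but as a total rather than per group: a repeated measures interaction with f = 0.25 and correlation 0.5, and a one-way ANOVA with 0.5 entered as f.

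**2. Power of a two-group comparison at the stated size** (two-sided t-test, d = 0.5)

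- 34 per group analysed: 52.9%.
- 27 per group: 43.8%.
- Effect detectable with 80% power: 0.690 SD at 34 per group (0.690 × 10.2 = 7.0 deg/s) and 0.777 SD at 27 per group (7.9 deg/s).

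**3. Power of the planned group-by-time test.** With two time points this is a two-sample test of change. If 10.2 is the SD of change, step 2 applies directly. If it is a cross-sectional SD, assumed equal at both times, with baseline to 16-week correlation r, then SD(change) = 10.2 × √(2(1 − r)) and the effective effect is 0.5 / √(2(1 − r)):

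| r | Effective d | Power, 27 per group | Power, 34 per group |
|---|---|---|---|
| 0.3 | 0.42 | 33% | 40% |
| 0.5 | 0.50 | 44% | 53% |
| 0.7 | 0.65 | 64% | 75% |
| 0.8 | 0.79 | 81% | 89% |

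The test reaches 80% at r of about 0.79 with 27 per group and about 0.74 with 34 per group.

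**4. Last value carried forward.** This keeps 34 per group in the analysis. If 20% carry forward no change, the mean effect becomes 0.8 × 0.5 = 0.4 SD, and power at 34 per group is about 37%, with the SD held constant and on the same basis as step 2.

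**The case against.** The strongest reply is that the planned analysis uses baseline data, so the unadjusted two-sample figure need not be the trial's true power. This stands. A reader might infer that actual power is 44–53% and that a real benefit would be missed about half the time. The document does not support that as a flat statement: depending on r, the group-by-time test at 27 to 34 per group ranges from 33–40% (r = 0.3) to 81–89% (r = 0.8). What the reply does not do is rescue the printed calculation, which invokes no correlation.

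A reader might also infer that the dropout sentence is simply false because a paired test was run with no allowance. The section names no test, so this is a guess. A one-sided paired test gives 27 and inflates to 34, and a between-group change-score test at r of about 0.79 would also need about 27 completers. The first conflicts with the two-tailed level and the second needs an unstated input. The supportable statement is that the allowance cannot be reconciled with the inputs as printed.

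Two further readings go too far. The lack of a separate calculation for Timed Up and Go, the other primary outcome, is something a condensed article may leave to the full protocol. The adequacy statement for secondary outcomes comes with no effect sizes or SDs, so it is unsupported but not shown to be wrong.

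That a full protocol or analysis plan may hold more detail does not answer the main point. The article prints a set of inputs and a result that does not follow from them for the comparison the trial makes.

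**Conclusion.** The power statement is wrong as written. For a two-group, two-sided 5% comparison at 0.5 SD and 80% power, the requirement is 64 evaluable or 80 randomised per group, against 34 stated to include dropout. The conclusion that 34 does not follow from the printed inputs rests on no assumption beyond the two-group design.

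The size of the power shortfall is conditional. The 44–53% range requires that 10.2 is the SD of change, or that it is cross-sectional with equal SDs and r about 0.5. A correlation of roughly 0.74 to 0.79 or higher would bring the planned test to 80%, but the article neither states nor relies on one. Carrying the last value forward keeps the analysed number at 34 without restoring power. This should be corrected because it concerns the power claimed for a primary outcome.

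**What to change.** Rewrite the Sample size paragraph, leaving recruitment unchanged:

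- Name the test used, say whether 10.2 is a cross-sectional SD or the SD of change, and state any assumed correlation with its source.
- Restate the power of the planned group-by-time test for 34 randomised and about 27 completing per group. If 10.2 is cross-sectional, at 27 per group for 0.5 SD this is 44% at r = 0.5, 64% at r = 0.7 and 81% at r = 0.8.
- Give the difference detectable with 80% power: about 0.69 SD (7.0 deg/s) at 34 per group and 0.78 SD (7.9 deg/s) at 27 per group, marked as applying to the unadjusted or r = 0.5 case.
- Note that carrying the last value forward does not recover lost power (about 37% at 34 per group under the no-change assumption above).
- Correct or withdraw the dropout-allowance sentence, and withdraw the adequacy statement for secondary outcomes unless figures are supplied to support it.

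If the sponsor prefers to quote baseline-adjusted ANCOVA power, with effective effect 0.5 / √(1 − r²), it is 55%, 71% and 85% at r = 0.5, 0.7 and 0.8 with 27 per group. The Statistical analysis section would first have to make ANCOVA the primary analysis in place of repeated measures ANOVA.

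The cost is one reworded paragraph and, unless a high correlation can be justified, a less favourable power statement. No additional participants are needed.

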### Missing data

Missing data (due to loss to follow up) will be imputed using the last value carried forwards method [35].

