**Methods/Design:**

A single blind randomized controlled trial will be conducted, with assessors blind to group allocation. Study participants will be aged 50 years and above, living in the community and have been identified as having impaired turning ability [outside of age and gender normal limits on the Step Quick Turn (180 degree turn) task on the Neurocom® Balance Master with long plate]. After a comprehensive baseline assessment, those classified as having balance impairment while turning will be randomized to intervention or control group. The intervention group will receive a 16 week individualized balance and strength home exercise program, based on the Otago Exercise Program with additional exercises focused on improving turning ability. Intervention group will attend four visit to the assessment centre over 16 weeks period, for provision, monitoring, modification of the exercise and encourage ongoing participation. Participants in the control group will continue with their usual activities. All participants will be re-assessed on completion of the 16 week program. Primary outcome measures will be the Step Quick Turn Test and Timed-Up and Go test. Secondary outcomes will include other clinical measures of balance, psychological aspects of falls, incidence of falls and falls risk factors.

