### Measures and procedures

Participants will undergo a comprehensive assessment including questionnaires consisting of socio-demographic, health and medical conditions, assessment of falls risk, psychological aspects associated with falls, level of physical activity as well as balance and mobility assessment using clinical and laboratory (force platform) tests. Questionnaires will be interspersed between the physical performance tests, and participants will be able to rest between tests if required. A summary of the screening and assessment measures to be used is shown in Table 1.

**Table 1 T1:** Summary of the screening and assessment measures during baseline and after 16 weeks intervention program

**Screening tests**	**Baseline**	**Follow-up (16 weeks)**
Questions: age; standing & walking; independent living; independent community ambulation with no more than single point stick	√	
Cognition (Elderly Cognitive Assessment Questionaire-ECAQ).	√	
Socio-demographic information	√	
Health conditions & medication use	√	
History of falls	√ (past 12 months)	Will be asked at each phone call follow up (preceding 3 weeks) and at 16 weeks (falls diary)

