### Intervention group activity

The intervention group will participate in a tailored (individualized) home based balance exercise program, provided by a trained researcher. This exercise program is based on the Otago program, a program shown to be effective in improving general balance in older people with mild balance dysfunction [29], but will include additional exercises selected to improve impairment of turning. The exercises selected for each participant in the intervention group will be based on assessment findings of areas of impairment. Two exercises of the 6–8 exercises prescribed will be selected to improve turning ability, while the other exercises will target other aspects of balance and mobility impairment based on the assessment findings. The selection of exercise and progression level will be tailored to the level of the participant ability. An exercise sheet will be provided by the researcher to each participant with illustrations and instructions detailing how to do the exercises, and dosage. The researcher will demonstrate each of the exercises and will ask the participant to perform the exercise just after the demonstration to ensure the participant understands how to do the exercise correctly. Participants will be provided with a written copy of the exercise program, and the researcher’s contact details if they need to discuss any aspect of the exercise program between visits. The home based exercise program is expected to take 20–30 minutes per session on average, including rests. Participants will be encouraged to continue the exercise program at least four times a week for the 16 weeks. The dosage is consistent with recommendations from a meta-analysis of exercise interventions in reducing falls [14]. In addition to the balance, strengthening and mobility related exercises, participants in the intervention group will also be provided with a graduated walking program, in which they will be asked to include a walking program 3 days/week, with gradually increasing distances.

Participants in the exercise intervention will return to the assessment laboratory for three occasions in the 16 week duration (one visit after 3, 6 and 9 weeks) to review the exercise program, modify exercises if required, and motivate the participant to persist with the exercises.

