### Follow up data collection

Intervention group participants will be asked to complete a daily log of their exercise participation, to be used to calculate exercise adherence. Both the intervention and control group will receive four phone calls interspersed over the 16 week period (weeks 4, 8, 12 and 16) by a researcher to obtain details regarding any falls that occurred between phone contacts.

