### Statistical analysis

Baseline and post intervention measures will be reported as means (m) ± standard deviations (SD). Data will be analysed on an intention to treat basis. Change in the selected primary outcome measure and secondary outcomes will be evaluated using two way Repeated Measures ANOVA to determine group main effect, time main effect, and interaction effect between group and time. Level of significance will be set at P < 0.05. Participants in the exercise intervention group will be grouped according to high adherence (> median adherence for the full group) and low adherence (≤ median adherence level). Repeated measures ANOVA will be used to determine whether there is a difference in change in the primary and secondary balance measures between the high adherence and low adherence group.

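### With one follow-up assessment, last value carried forward enters every dropout with zero change; this shrinks a real effect and, if dropout differs by arm, can bias the estimate in either direction

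*Protocol article*

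**What the plan says.** The Missing data section is a single sentence: "Missing data (due to loss to follow up) will be imputed using the last value carried forwards method". The article names no other method and no sensitivity analysis.

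The schedule provides one post-baseline measurement. The abstract says "All participants will be re-assessed on completion of the 16 week program", and Table 1 is titled "Summary of the screening and assessment measures during baseline and after 16 weeks intervention program". It lists Step Quick Turn and Timed Up and Go at those two times only. The contacts in between supply no balance or mobility value:

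- The laboratory returns in the intervention arm are described as "one visit after 3, 6 and 9 weeks) to review the exercise program, modify exercises if required" (Intervention group activity).
- The phone calls to both arms are "to obtain details regarding any falls that occurred between phone contacts" (Follow up data collection).

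Under Statistical analysis, the model is "two way Repeated Measures ANOVA to determine group main effect, time main effect, and interaction effect between group and time", and "Data will be analysed on an intention to treat basis". Under Sample size, on loss to follow-up: "This calculation includes allowance for an anticipated 20% dropout rate". No split by arm is given.

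**The concern.** Carrying a value forward presupposes a series of measurements. Here there is only the baseline value to carry, so the rule amounts to assuming that nobody who is lost would have changed at all. About 14 of 68 participants (20% of 68 = 13.6) would be entered that way.

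That assumption is doubtful in this trial. Participants enter because their turning test is outside normal limits, and everyone is retested on the same equipment. Some improvement unrelated to exercise is therefore plausible in both arms, from retest learning or regression to the mean. Only one arm is asked to exercise for 16 weeks, so unequal loss is also plausible. When both occur, the arm that loses more people is given more zeros, and that alone moves the treatment contrast. Single imputation also treats the filled-in values as if they had been observed. The primary estimate, its power and its error rate are all affected.

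**Working it through.** **Inputs from the protocol article.** 34 per group; SD 10.2 deg/s and effect size 0.5, so the planned effect is 0.5 × 10.2 = 5.1 deg/s; two-sided 0.05; 20% dropout overall (all from Sample size). Lower sway is better, so a benefit is negative. The article gives no figure for the effect of the imputation rule, so there is none to reproduce. Whether 34 per group follows from the stated inputs is a separate question; 34 is taken as given here.

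**Assumed inputs, not in the article.** Correlation of 0.6 between baseline and 16 weeks, so the SD of change is 10.2 × √(2 × (1 − 0.6)) = 9.1. Common improvement in both arms of 3 to 6 deg/s. Dropout splits of 20%/20%, 30%/10% and 10%/30% (exercise/control). Dropout is unrelated to outcome.

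**Step 1: what is tested.** With two time points, the group-by-time interaction is equivalent to a t-test on change. The imputed zeros go straight into it.

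**Step 2: expected contrast.** With mean change mT and mC and dropout dT and dC:

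expected estimate = (1 − dT)·mT − (1 − dC)·mC

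The true contrast is mT − mC, so the bias is dC·mC − dT·mT.

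**Step 3: true effect of -5.1, common improvement of 3 (mT = -8.1, mC = -3).**

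- 20%/20%: 0.8 × (-8.1) − 0.8 × (-3) = -6.48 + 2.40 = -4.08. A fifth of the effect is lost.
- 30%/10%: 0.7 × (-8.1) − 0.9 × (-3) = -5.67 + 2.70 = -2.97.
- 10%/30%: 0.9 × (-8.1) − 0.7 × (-3) = -7.29 + 2.10 = -5.19. The effect is slightly overstated.

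**Step 4: no true effect.**

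- 30%/10%, common improvement 3: 0.7 × (-3) − 0.9 × (-3) = +0.6, against exercise.
- 30%/10%, common improvement 6: 0.7 × (-6) − 0.9 × (-6) = +1.2, against exercise.
- 10%/30%: the same sizes with the sign reversed, in favour of exercise.
- Equal dropout, or no change in either arm: 0.

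**Step 5: power and type I error, by simulation.** The comparator is a change-score t-test on participants with observed 16-week data, so only the handling of missing values differs.

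| Scenario | Estimate, carried forward | Rejection rate, carried forward | Rejection rate, observed data |
|---|---|---|---|
| Effect -5.1, common 3, 20%/20% | -4.1 | 49% | about 53% |
| Effect -5.1, common 3, 30%/10% | -3.0 | 28% | about 52% |
| No effect, common 3, 30%/10% | 0.6 | about 6% | about 5% |
| No effect, common 6, 30%/10% | 1.2 | about 9% | about 5% |
| No effect, common 6, 20%/20% | 0 | about 5% | about 5% |

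The observed-data estimates were about -5.1 and 0 throughout. Power falls only a little at 20%/20% because the zeros also reduce the variance of change.

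**The case against.** No one can dispute from the schedule that the carried value is baseline. The objections concern how far the consequences reach, and several stand.

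- **The bias is conditional.** A reader might infer that the rule always distorts the result. It does not: there is no bias if neither arm changes, or if dropout is equal and there is no effect. A false difference needs both unequal dropout and non-zero change, and the article documents neither.
- **The more obvious split works against exercise.** A reader might infer that the rule favours the intervention. If the exercise arm loses more people, as its burden suggests, the error is conservative. A false benefit needs heavier loss in the control arm, which is possible but which nothing in the article predicts.
- **Regression to the mean is not certain.** Under Participants, screening takes place on an occasion before baseline. If the selecting turn test is then repeated at baseline, much of the regression is over before the carried value is recorded. The abstract and Table 1 point instead to selection at baseline. The article does not say whether sway or turn time must be abnormal, and Timed Up and Go is not a selection test. Practice trials and averaging over three trials limit learning and measurement error.
- **Larger figures are easy to produce.** Setting about 60% power for ANCOVA on observed data against 28% mixes the gain from baseline adjustment with the loss from imputation; like for like it is 52% to 28%. The 9% type I error needs a common improvement of 6 deg/s, more than the planned effect of 5.1; with 3 deg/s it is about 6%.
- **Missing at random is also an assumption.** People who stop exercising may not improve, and a missing-at-random analysis may credit them with completers' gains. This is a reason to keep the zero-change analysis as a check, but not as the only analysis.

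None of this changes the fact that the article fixes zero change for dropouts as its one rule. The point is a stated choice, not detail left to a statistical analysis plan.

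**Conclusion.** The concern holds in conditional form. That every lost participant is scored as unchanged follows from the visit schedule alone. At the protocol's own 20% dropout, if equal by arm and if those lost would have changed like those who stay, a real effect shrinks by a fifth (-5.1 to about -4.1 deg/s) at a cost of about 4 points of power. If dropout differs by arm and the arms also change for reasons other than exercise, the estimate can be biased in either direction. At an assumed 30%/10% split, -5.1 becomes about -3.0 with a common improvement of 3, and under no effect the type I error is about 6% to 9% for common improvements of 3 to 6.

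These figures rest on the assumed correlation, splits and common improvement, and on dropout unrelated to outcome. The documents do not support a claim that the rule will create a false benefit, only that it gives no protection against a distorted estimate.

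**What to change.** Replace last value carried forward as the primary method, for both primary outcomes and the other measures taken at baseline and 16 weeks. Either of these would do:

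- a baseline-adjusted likelihood analysis: a mixed model with a common baseline mean, or ANCOVA on the observed 16-week values; or
- multiple imputation by arm, using the baseline outcome, age and sex.

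Keep last value carried forward as a sensitivity analysis, described plainly as zero change for dropouts, and report dropout by arm beside it.

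The cost is one paragraph of analysis text and routine software, with no new data and no burden on participants. The downside is that the new primary analysis assumes missingness at random and may be generous to people who stop exercising. The retained zero-change analysis shows how much the conclusion depends on that.
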